| B | On how many of the last SEVEN DAYS did you do **moderate activities** for **at least 30 minutes**, such as recreational swimming; gardening; heavy cleaning such as washing windows, vacuuming, sweeping or mopping; brisk walking; biking at moderate pace; etc.?  0 1 2 3 4 5 6 7 | └──┘ | PA_1b |

| **SECTION 7: BEHAVIOURAL MEASURES – TOBACCO USE** | | | |
| --- | --- | --- | --- |
| **S.NO:** | **Question** | **Response** | **Code** |
| A | Have you used any tobacco products, such as cigarettes, cigars, pipes, chewing tobacco or snuff/snus in the last 7 days?  1. Daily  2. Less than daily  3. Never  **If ‘never’, SKIP to SECTION 8** | **└──┘** | TOB_1a |
| B | During any visit to a doctor or other health worker in the PAST 12 MONTHS, were you **advised to quit** using tobacco?  Yes = 1  No = 0  Zero visits during the past 12 months = 3 | **└──┘** | TOB_1b |

| **SECTION 8: BEHAVIOURAL MEASURES – ALCOHOL CONSUMPTION** | | | |
| --- | --- | --- | --- |
| **S.NO:** | **Question** | **Response** | **Code** |
| A | During the PAST MONTH, **how frequently** have you had at least one standard alcoholic drink? *(USE SHOWCARD 6)*  1 = Daily = 1  2 = 5-6 days per week  3 = 2-4 days per week  4 = 1-2 days per week  5 = 1-3 days per month  6 = Occasionally, usually less than once a month  7 = Never | **└──┘** | ALC_1a |

| **SECTION 9: OTHER BEHAVIOURAL MEASURES – FOOT CARE**  **For participants with pre-diabetes, SKIP to SECTION 10** | | | |
| --- | --- | --- | --- |
| **S.NO:** | **Question** | **Response** | **Code** |
| A | On how many of the last SEVEN DAYS did you check your feet for sore/ulcers?  0 1 2 3 4 5 6 7 | **└──┘** | FOOT_1a |

| **SECTION 10: BIOCHEMICAL** | | | |
| --- | --- | --- | --- |
| **S.NO:** | **Question** | **Response** | **Code** |
| **BIOCHEMICAL – FPG** | | | |
| A | During the past 12 hours have you had anything to eat or drink other than plain water  Yes = 1  No = 0  *(To be asked when collecting FPG for diagnosis/recruitment)* | **└──┘** | FPG_1a |
|  | If yes, do not proceed |  | inst_fpg1 |
| B | Choose the units appropriate for the device measuring the fasting blood glucose  *(Essential that fasting sample collected, do not proceed if participant has not fasted)* | 1. mmol/L  2. mg/dL | FPG_1b_opt |
|  | Fasting blood glucose measure (mmol/L) | └─┴─┘**. └─┘**mmol/L | FPG_1b |
|  | Fasting blood glucose measure (mg/dL) | └─┴─┴─┘**. └─┘**mg/dL | FPG_1b_units |
| **BIOCHEMICAL – HBA1C** | | | |
| A | Choose the units appropriate for the device measuring the  glycated haemoglobin concentration Test 1  (% or mmol/m) | 1. Percent (%)  2. mmol/m | hba1c_1a_opt |
|  | Glycated haemoglobin concentration Test 1 (%) | └─┴─┘**. └─┘**% | HBA1C_1a |
|  | Glycated haemoglobin concentration Test 1 (mmol/m) | └─┴─┴─┘**.└─┘**mmol/mol | HBA1C_1a_units |

| **SECTION 11: ANTHROPOMETRY AND OTHERS: HEIGHT, WEIGHT & WAIST CIRCUMFERENCE** | | | |
| --- | --- | --- | --- |
| **S.NO:** | **Question** | **Response** | **Code** |
| **Section 11.1: ANTHROPOMETRY** | | | |
| A | Height | in Centimetres (cm) └─┴─┴─┘ | HT_1 |
| B | Weight | in Kilograms (kg) └─┴─┴─┘.└─┘ | WT_1 |
| C | Waist circumference | in Centimetres (cm) └─┴─┴─┘.└─┘ | WC_1 |
| **Section 11.2: BLOOD PRESSURE (SITTING)**  *(Spread the 3 measurements throughout the total time used for the data collection of this patient – usually with a 10-min gap in-between)* | | | |
| A | Blood pressure, reading 1 | Systolic (mmHg) └─┴─┴─┘ | SBP_1a |
|  |  | Diastolic (mmHg) └─┴─┴─┘ | DBP_1a |
| B | Blood pressure, reading 2 | Systolic (mmHg) └─┴─┴─┘ | SBP_1b |
|  |  | Diastolic (mmHg) └─┴─┴─┘ | DBP_1b |
| C | Blood pressure, reading 3 | Systolic (mmHg) └─┴─┴─┘ | SBP_1c |
|  |  | Diastolic (mmHg) └─┴─┴─┘ | DBP_1c |
| **Section 11.3: 7-DAY PEDOMETER STEPS**  ***(****Blind the number of steps displayed by the pedometer using a masking tape.*  *Separate procedure about pedometers in each country to be made by country teams:*  *Clear instruction about pedometer at the time of handing out to participants: only complete days, wear it the whole day!*  *If not complete 7 days: still write down the measurements. Re-do only if participant is willing.*   - *Number of minimum complete days required (5?) – to be considered.* | | | |
| A | Period of pedometer recording  *(Enter only completed days)* | Start date: DD/MM └─┴─┘/└─┴─┘  End date: DD/MM └─┴─┘/└─┴─┘ | PED_1a_start  PED_1a_end |
| B | Total pedometer steps recorded by the device for the period | └─┴─┴─┴─┴─┘ | PED_1b |

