## 3.5 Study Participants:

Participants will be residents within the identified catchments areas at each of the study sites as described above. Eligible subjects will be:

1. current residents who have resided in their respective communities for at least 6 months prior to enrollment into the study,
2. aged 30 – 75 years,
3. currently not known to be pregnant
4. have no plans of migrating out of the study area over the next 12 months from the date of enrollment into the study,
5. able to provide written informed consent,
6. agree to allow home visits and follow-up contacts as part of participating in the trial,
7. no previous diagnosis with diabetes, or diagnosis of diabetes of no longer than 12 months prior to being screened for enrollment into the study
8. have a positive confirmatory test of pre-diabetes or diabetes

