**3.6.2.** **Facility recruitment**

Recruitment will take place at the two selected facilities. Persons presenting at the facilities who are either diagnosed with T2DM, or present with NCDs risk factors, including obesity, high blood pressure and/or impaired glucose tolerance, will be invited to participate in the trial. They will be recruited when visiting the facility for routine clinical care or upon referral from the community as per the above outlined protocol. Subjects will be classified as diabetic if two consecutive FPG tests > 6.9 mmol/L and as pre-diabetic if two consecutive FPG tests are between 6.1-6.9 mmol/L. A third FPG test may be needed to validate different test results (Figure 13 and Table 13).

Following eligibility confirmation, an ‘Eligibility Confirmation Form’ will be administered and written informed consent sought from the subject prior to study enrollment. Briefly, the study manager at the health facility will provide information on SMART2D study objectives, procedures, benefits and risks of participating, as well as confidentiality issues. Participants will receive a consent form and continue to receive standard medical care as needed, and as available at the health facility. Administration of any study procedures will only happen after eligible subjects have consented to participate in the study, upon which they will be enrolled and given a unique study number.

*Figure 13 Algorithm for sequence of screening tests for South Africa*

[figure not shown]

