## 3.13 Statistical analysis Plan

### 3.13.1 Primary intervention efficacy analysis:

We will use intention-to-treat analyses for all primary outcomes, that is, all participants will be analyzed as assigned to their respective study arms. Since the unit of analysis for the primary outcome of interest are the individual participants, to minimize the effect of within cluster correlations, we will employ generalized estimating equations (GEEs) to evaluate changes over time in HbA1c values as a continuous variable among participants with pre-diabetes; and the proportion of participants with stabilized plasma glucose among participants with diabetes, in relation to assigned trial arm. Thus we use multivariable linear regression mixed effects modeling with a random intercept, unstructured correlation matrix and robust standard errors, to evaluate changes over time in HbA1c, and logistic regression analysis to compare the proportion of participants with stabilized plasma glucose among participants with diabetes.

Missing data are expected due to missed appointments, drop-outs, loss-to-follow-up and/or death. One technique to deal with missing data when the outcome is continuous, is hierarchical linear modeling (HLM; also called random effects regression) [Singer et al. 2003].

We do not anticipate differences in the intercept within each site, as randomization is expected to balance out baseline differences between the groups. However, there may be differences in the intercepts between sites, reflecting differences within the client populations in each site. We anticipate that the primary factor affecting the slope (i.e., the rate of change of the outcome measure) will be group membership (i.e, facility only or facility plus community intervention). If there is any significant unexplained variance after baseline differences and site membership have been accounted for, we can look for other factors influencing the slope, such as sex, age, co-morbidities, etc. Another analytic option that will be considered is generalized estimating equations (GEE) [Zeger et al. 1986], which can adjust for clustered, serially correlated data with missing values. The choice of techniques will be based on the nature of the data.

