|  | - Make appropriate changes to translated tools. - This is final version to be administered once questions are clarified. |

INSTRUCTIONS to site teams

- This set of data collection tools contains all the generic instruments that should be used during screening/recruitment and baseline.
- All sections are numbered. Kindly do not change the section numbers, question numbers or codes in this version.
- Please provide laminated SHOWCARDS in colour to all data collectors. Instruct data collectors to give the appropriate SHOWCARD for each section to the participant to make it easier for them to respond.
- It is recommended that baseline data collection is staggered over two occasions to decrease participant fatigue and improve the quality of the data collected. Please follow the recommended steps below to divide the baseline data collection in two steps.
  - **During RECRUITMENT visit**

STEP 1 = Section 1 to confirm eligibility 🡺 Sign informed consent 🡺 Section 2 to assign identifiers 🡺 Sections 2-11.2 🡺 Fill in start date for pedometer reading in Section 11.3 🡺 Give instructions on pedometer use + demonstrate use of pedometer + reset and help the participant to wear a masked pedometer 🡺 Confirm instructions and decide on date to collect back the pedometer after 7 days 🡺 If you are unable to collect back the pedometer after 7 days – give specific instructions on what the participant is expected to do 🡺 BREAK off baseline data collection HERE.

- - **During visit to COLLECT PEDOMETER**

STEP 2 = Meet on previously decided date 🡺 Check pedometer and enter reading and end-date in section 11.3 🡺 Complete sections 12-21. END of BASELINE data collection.

About this document

This is a master document containing the complete set of data collection tools that will be administered using a survey methodology. Please note, that evaluations that involve qualitative methodologies are not included here.

The document is divided into four parts:

*Part I: Basic participant data*

*Part II: Intervention process measures (based on Self Determination Theory)*

*Part III: Selected context measures and expenditure*

*Part IV: Process and fidelity checks*

Please note that this document includes tools pertaining to individuals, facilities and local community. It is not meant to be administered together in one visit. Part I includes the set of tools that should be administered together in one baseline/end-line visit.

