| **STEP 2** | **Answer the following ELIGIBILITY questions** | **No** | **Yes** |  |
| a) | Has the individual been a resident in the location of the interview for less than 6 months? | └──┘ | └──┘ | ELI_2a |
| b) | Is the individual less than 30 years, or older than 75 years of age | └──┘ | └──┘ | ELI_2b |
| c) | Has the individual indicated that he/she has plans of migrating out of the study area over the next 12 months? | └──┘ | └──┘ | ELI_2c |
| **For participants with pre-diabetes, SKIP to (e)** | | | | |
| d) | Was the individual diagnosed with diabetes longer than 12 months before being screened for the SMART2D intervention trial?  REDCAP: "FOR INTERVIEWERS: If the participant has pre-diabetes, mark the selection 'Participant has pre-diabetes'" | 0 = No  1 = Yes  2 = Participant has pre-diabetes | | ELI_2d |
| e) | If female, is the individual pregnant?  **If male, SKIP to (f)**  REDCAP: "FOR INTERVIEWERS: If the participant is male, mark the selection Participant is male" | 0 = No  1 = Yes  2 = Participant is male | | ELI_2e |
| f) | Has the individual been diagnosed with heart disease, stroke or peripheral vascular disease/serious mental disorders affecting cognitive functions? | └──┘ | └──┘ | ELI_2f |
| g) | Has any other individual in the same household been enrolled in this study? | └──┘ | └──┘ | ELI_2g |
| h) | Is the individual enrolled in any other study related to diabetes/ self-management | └──┘ | └──┘ | ELI_2h |
| 🡺 If all of the responses in STEP 2 are NO, the subject is ELIGIBLE to be recruited for the trial. If more than one individual in a household is found eligible, apply the KISH methodology (See Appendix 1). | | | | inst_eli_2 |

| **SECTION 2: IDENTIFICATION INFORMATION**  (Instruction: To be included in each set of participant questionnaires) | | | |
| --- | --- | --- | --- |
| **S.NO:** | **Questions** | **Response** | **Code** |
| A | Site Identification Number  UG/SA/SW | └──┘└──┘ | SI_ID |
| B | Cluster/facility Identification number  *Each site to assign numbers to each cluster (SA: 1-2, SW: 1-4, UG: 1-9)* | └──┘ | CL_ID |
| C | Trial arm identification code | 1= Facility only  2 = Facility + community └──┘  3 = No intervention (Uganda only) | TA_ID |
| D | Unique Participant ID number *(Assigned by study team in the field - assign a range of numbers to each cluster)* | └──┘└──┘└──┘ | PA_ID |
| E | To which diagnostic group is the participant recruited? | 1 = Diabetes  2 = Pre-diabetes └──┘ | DX_ID |

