| **SECTION 4: MEDICAL AND MEDICATION HISTORY** | | | | |
| --- | --- | --- | --- | --- |
| **S.NO:** | **Questions** | | **Response** | **Code** |
| A | Have you ever been told by a doctor or other health worker that you have raised blood pressure or hypertension?  No = 0  Yes = 1  Don’t know/unsure = 777 | └──┘ | | MED_1a |
| B | Have you ever taken any drugs (medication) for raised blood pressure prescribed by a doctor or other health worker?  No = 0  Yes = 1  Don’t know/unsure = 777  *Ask the participant to only consider drugs for raised blood pressure prescribed by a doctor or other health worker (if possible interviewer to observe medication for confirmation)* | └──┘ | | MED_1b |
| C | Have you ever been told by a doctor or other health worker that you have raised blood sugar or diabetes?  No = 0  Yes = 1  Don’t know/unsure = 777 | └──┘ | | MED_1c |
| D | Have you ever been told by a doctor or other health worker that you have kidney disease?  No = 0  Yes = 1  Don’t know/unsure = 777 | └──┘ | | MED_1d |
| E | Have you developed any foot ulcers in the past year?  No = 0  Yes = 1  Don’t know/unsure = 777 | └──┘ | | MED_1e |
| F | Have you had any loss of vision in the past year?  No = 0  Yes = 1  Don’t know/unsure = 777 | └──┘ | | MED_1f |
| **For participants with pre-diabetes, SKIP to J** | | | | |
| G | Are you currently on any injectable insulin?  No = 0  Yes = 1  Don’t know/unsure = 777  If, NO, skip to I | └──┘ | | MED_1g |
| H | Are you currently on any injectables other than insulin?  No = 0  Yes = 1  Don’t know/unsure = 777 | └──┘ | | MED_1h |
| I | Are you currently on any oral hypoglycemic agents  No = 0  Yes = 1  Don’t know/unsure = 777 | └──┘ | | MED_1i |
| J | Are you currently on any traditional or complementary medicines to treat or prevent diabetes or pre-diabetes?  No = 0  Yes = 1  Don’t know/unsure = 777 | └──┘ | | MED_1j |

| **SECTION 5: BEHAVIOURAL MEASURES – DIET** | | | | | |
| --- | --- | --- | --- | --- | --- |

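### The baseline form does not reliably separate newly found from previously diagnosed diabetes and skips a drug item; the diabetes responder model should adjust for treatment and diagnosis at entry

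*Protocol*

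**What the plan says.** - **Eligibility.** Section 3.5 admits people with "no previous diagnosis with diabetes, or diagnosis of diabetes of no longer than 12 months prior to being screened". Everyone also needs a positive confirmatory test.
- **Eligibility check (ELI_2d).** The form asks "Was the individual diagnosed with diabetes longer than 12 months before being screened for the SMART2D intervention trial". The answer No (code 0) fits both a person never diagnosed and one diagnosed within the year.
- **Medical history (MED_1c).** The form asks "Have you ever been told by a doctor or other health worker that you have raised blood sugar or diabetes", answered yes, no or unsure, with no date.
- **Order of data collection.** The instructions to site teams begin the recruitment visit with "STEP 1 = Section 1 to confirm eligibility"; consent and the later sections, including medical history, follow.
- **Drug items.** Item G (MED_1g) asks about insulin and sends a No to item I. Item H (MED_1h) is "Are you currently on any injectables other than insulin". Item I (MED_1i) is "Are you currently on any oral hypoglycemic agents".
- **Recruitment.** Section 3.6 places cluster randomisation before participant screening. In South Africa, facility recruitment invites "Persons presenting at the facilities who are either diagnosed with T2DM, or present with NCDs risk factors".
- **Analysis.** Section 3.13.1 plans "logistic regression analysis to compare the proportion of participants with stabilized plasma glucose among participants with diabetes". It names no covariates for that model.

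**The concern.** The diabetes outcome in section 3.9 counts a participant as a responder if month-12 HbA1c is below 53 mmol/mol or 5 mmol/mol under baseline. Treatment history can affect both routes. Someone untreated at entry may fall on first treatment in any arm. Someone already treated may have had part of that fall before baseline. If the arms enrol different mixes of the two, an unadjusted comparison can credit the difference in mix to the intervention, or hide a real effect.

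Section 3.13.1 expects randomisation to balance baseline differences within each site. That is a weak expectation with so few clusters and with participants recruited after allocation. Recruitment is also partly arm-specific: under section 3.3.3.1, community mobilisation is meant to raise interest in joining the trial, and its materials are handed out at screening events in the facility-plus-community arm. The mix could therefore differ systematically as well as by chance.

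**Working it through.** **1. What the form can and cannot tell apart**

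| Participant with diabetes | ELI_2d | MED_1c | MED_1g / MED_1i |
|---|---|---|---|
| Found by screening, untreated | No | Yes possible, if told of the result | No / No |
| Diagnosed within 12 months, untreated | No | Yes | No / No |
| Diagnosed within 12 months, on insulin or oral agents | No | Yes | Yes to at least one |
| Diagnosed within 12 months, only on a non-insulin injectable | No | Yes | No / No; MED_1h never asked |

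The third row is identifiable. The first two are not reliably separable. MED_1c also accepts raised blood sugar short of diabetes, so a Yes is not proof of a prior diabetes diagnosis. The fourth row is lost only because of the skip at G.

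**2. Clusters per arm.** Section 3.10 gives 9 (Uganda), 4 (Sweden) and 2 (South Africa). With equal allocation (assumed) over 3, 2 and 2 arms, that is 9/3 = 3, 4/2 = 2 and 2/2 = 1.

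**3. The plan's own benchmark.** Section 3.10 states a 2-point difference (30% and 32%) and 58 per arm before clustering. The formula is not legible in the text, so I assume the usual unpooled form:

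n = (1.960 + 0.842)² × [0.30×0.70 + 0.32×0.68] / 0.02² = 7.849 × 0.4276 / 0.0004 ≈ 8,391.

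So 58 does not follow from 2 points. It does follow from 30% against 55%: 7.849 × (0.21 + 0.2475) / 0.25² = 57.5, rounded up to 58. This is a separate fault. It matters here only because it makes the 2 points a poor yardstick.

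**4. Shift in the unadjusted difference.** Shift = (arm difference in the share with a given history) × (difference in response rate between histories). The documents give neither input; both are assumed.

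| Imbalance in mix | Gap 10 points | Gap 20 points | Gap 30 points |
|---|---|---|---|
| 10 points | 1 | 2 | 3 |
| 20 points | 2 | 4 | 6 |
| 30 points | 3 | 6 | 9 |

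**5. How large a chance imbalance could be.** Two sets of assumptions:

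- If the untreated share varies between facilities with SD 15 points, the SD of the arm difference is 0.15 × √(2/k). For k = 3 this is 0.122 and for k = 1 it is 0.212. At a 30-point gap the shifts are 3.7 and 6.4 points.
- SD = √{2q(1−q)[1 + (m−1)ρ]/n}, with a previously diagnosed share q of 20–40%, ICC of the mix ρ of 0.02–0.10, n = 128, 81 and 136 per arm (section 3.10; Sweden before doubling), and m = n/k. South Africa's upper end: √{2 × 0.24 × (1 + 135×0.10)/136} = 0.226. The ranges are 6.8–13.9 points (Uganda), 8.4–17.1 (Sweden) and 9.3–22.6 (South Africa). At a 20-point gap, one SD shifts the difference by 1.4–2.8, 1.7–3.4 and 1.9–4.5 points.

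**The case against.** A reader might infer that the form cannot tell the groups apart at all, that the model ignores treatment at entry, and that imbalance passes straight into the primary result. The documents do not support this.

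- **Treatment is largely recorded.** MED_1g and MED_1i are asked of everyone in the diabetes group, and the harm argued is mainly treated versus untreated. This stands; the gap is narrower than total inability to separate. Nor will every newly found person answer Yes to MED_1c: in Uganda the first two tests are done at home by field research assistants, while the item refers to a doctor or health worker.
- **The model is silent.** No covariate is listed for the logistic model and none is excluded; a list may sit in an analysis plan that is not at hand. This stands, so adjustment is an improvement to specify, not a proven omission. The section's mention of baseline differences and other factors concerns the slope of the continuous outcome.
- **Entry criteria narrow the gap.** The confirmatory test keeps out treated people already below the diabetes thresholds. This stands, and the assumed gaps do not allow for it.
- **Chance imbalance is sampling error.** A sound cluster analysis should carry it in its standard error. That is right in principle. It does not cover a systematic difference in recruitment between arms, and one facility per arm allows no between-facility variance to be estimated within South Africa.
- **Cluster counts.** Section 3.6.3 describes allocation of postal-code zones in Sweden, so two units per arm there is uncertain.
- **An unseen form may record the diagnosis date.** Uganda's short screening form is not shown. But the site instructions say the set holds all generic instruments for screening, recruitment and baseline, so this is a weak rescue.

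**Conclusion.** The form faults are plain on the page. Prior diagnosis is not reliably captured, and non-insulin injectables are never asked of people who answer No to insulin. The skip error works identically in all arms, so it does not bias the comparison; its effect is to misclassify a few treated people as untreated.

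The consequence for the primary diabetes comparison is conditional. It needs both a real difference in mix between arms and a real difference in response by history, and neither is given. Under assumed values of 10 to 30 points each, the shift is 1 to 9 points. Many of these values equal or exceed the stated 2-point design difference, but most are small beside the roughly 25 points that 58 per arm can detect. Recruitment after allocation, the small number of clusters, and enrolment of already diagnosed clinic patients in South Africa make an imbalance plausible enough to guard against.

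**What to change.** 1. Reword MED_1c to ask whether, before being screened for this study, the participant had been told by a doctor or other health worker that they have diabetes, and if so in which month and year. Leave raised blood sugar out of this item.
2. Change the skip at item G so that No leads to H.
3. In section 3.13.1, state that the diabetes responder model includes baseline glucose-lowering treatment (none / any, from MED_1g to MED_1i) and prior diagnosis (yes / no) as fixed covariates. Add that in South Africa, with one facility per arm, this reduces but cannot remove confounding.

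The cost is one reworded item with a date field, one corrected skip and a short addition to the analysis section, with no added participants or procedures. Where baseline forms are already complete, treatment from MED_1g and MED_1i can still be used; timing of diagnosis would be hard to recover.

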| The next questions ask about the fruits and vegetables that you usually eat. I have a nutrition card here that shows you some portion sizes of the foods we are talking about. Each picture represents the size of a serving. As you answer these questions please think of a TYPICAL WEEK and a TYPICAL DAY in the LAST MONTH.  *(Use the SHOW CARDS provided - Important for interviewers to show the right card for the right question as indicated: so for whole fruit – show card 1, for cut fruits show card 2, etc. Each show card represents 1 serving of the food indicated.)* | | | | | inst_diet1 |
| **S.NO:** | **Question** | | **Response** | **Code** | |
| A | In a typical week, on how many days do you eat **fruit**?  Don’t know 777 | | Number of days└─┴─┘ *If zero, go to C* | DIET_1a | |
| B | 1. How many servings of **whole fruit** do you eat on a typical day? (SHOWCARD 1)  Don’t know 777  2. How many servings of **cut or small fruit (fresh or frozen)** do you eat on a typical day? (SHOWCARD 2)  Don’t know 777  3. How many servings of **canned fruit** do you eat on a typical day? (SHOWCARD 2)  Don’t know 777  4. How many servings of **dried fruits** do you eat on a typical day? (SHOWCARD 4) | | Number of servings:  1. └─┴─┘.└─┴─┘  2. └─┴─┘.└─┴─┘  3. └─┴─┘.└─┴─┘  4. └─┴─┘.└─┴─┘ | DIET_1b1,2,3,4 | |
| C | In a typical week, on how many days do you eat **vegetables** like tomatoes, carrots, onions, etc. (excluding tubers and high starch vegetables such as cassava, potatoes, matoke, yams, sweet potatoes)?  Don’t know 777 | | Number of days └─┴─┘ *If zero, go to E* | DIET_1c | |
| D | 1. How many servings of **cut vegetables (fresh or frozen)** do you eat on a typical day?  (SHOWCARD 2)  Don’t know 777  2. How many servings of **canned vegetables** do you eat on a typical day? (SHOWCARD 2)  Don’t know 777  3. How many servings of **uncooked leafy vegetables** do you eat on a typical day?  (SHOWCARD 1) | | Number of servings:  1. └─┴─┘.└─┴─┘  2. └─┴─┘.└─┴─┘  3. └─┴─┘.└─┴─┘ | DIET_1d1,2,3 | |
| E | In a typical week, how many days do you eat **tubers and high starch vegetables (**such as cassava, potatoes, matoke/plantain, yams, sweet potatoes)?  Don’t know 777 | | Number of days└─┴─┘ *If zero, go to G* | DIET_1e | |
| F | How many servings of **tubers and high starch vegetables** do you eat on one of those days? (Such as cassava, potatoes, matoke/plantain, yams, sweet potatoes) (SHOWCARD 1)  Don’t know 777 | | Number of servings└─┴─┘.└─┴─┘ | DIET_1f | |

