| G | In a typical week, how many days do you eat **refined starch products**, (such as white rice, pasta, white breads, maize meal, cassava flour meal, pap)?  Don’t know 777 | | Number of days└─┴─┘ *If zero, go to K* | DIET_1g | |
| H | 1. "How many servings of bread do you eat on a typical day?" (SHOWCARD 3)  Don’t know 777  2. "How many servings of other refined starch products (such as white rice, pasta, maize meal pap) do you eat on a typical day?” (SHOWCARD 1)  Don’t know 777 | | Number of servings:   1. └─┴─┘.└─┴─┘ 2. └─┴─┘.└─┴─┘ | DIET_1h1,2 | |
| I | In a typical week, how many days do you eat **non-refined starch** (such as brown rice, whole grain pasta, wholegrain cereal, samp or whole meal/whole wheat / brown breads)?  Don’t know 777 | | Number of days└─┴─┘ *If zero, go to M* | DIET_1i | |
| J | 1. "How many servings of non-refined bread do you eat on a typical day?" (SHOWCARD 3)  Don’t know 777  2. "How many servings of other non-refined starch products (such as brown rice, whole grain pasta, wholegrain cereal, samp or whole meal) do you eat on a typical day?" (SHOWCARD 1)  Don’t know 777 | | Number of servings:   1. └─┴─┘.└─┴─┘ 2. └─┴─┘.└─┴─┘ | DIET_1j1,2 | |
| K | In a typical week, how many days do you eat **fish**?  Don’t know 777 | | Number of days└─┴─┘ *If zero, go to O* | DIET_1k | |
| L | How many servings of **fish**, do you eat on one of those days?  (SHOWCARD 3)  Don’t know 777 | | Number of servings└─┴─┘.└─┴─┘ | DIET_1l | |
| The next questions ask about the way you most often prepare different types of food in your household. | | | | | |
| M | Which cooking method do you usually use when preparing chicken?  1 = Grill/Oven/Roast  2 = Fry  3 = Boil  4 = Steam  5 = Other (specify) | | └──┘  If 5, please specify  **_____________________** | DIET_1m  DIET_1m_other | |
| N | Which cooking method do you usually use when preparing other meat?  1 = Grill/Oven/Roast  2 = Fry  3 = Boil  4 = Steam  5 = Other (specify) | | └──┘  If 5, please specify  **___________________** | DIET_1n  DIET_1n_other | |
| O | Which cooking method do you usually use when preparing fish?  1 = Grill/Oven/Roast  2 = Fry  3 = Boil  4 = Steam  5 = Other (specify) | | └──┘  If 5, please specify  **___________________** | DIET_1o  DIET_1o_other | |

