| P | Which cooking method do you usually use when preparing vegetables?  1 = Grill/Oven/Roast  2 = Fry  3 = Boil  4 = Steam  5 = Other (specify) | | └──┘  If 5, please specify  **___________________** | DIET_1p  DIET_1p_other | |
| The next questions ask about the oil or fat that is most often used for meal preparation in your household, and about meals that you eat outside a home. | | | **How often** do you use the following **oils and fats** in your household? | inst_diet3 | |
| Q | | Use the scale below:  1 = Daily  2 = 5-6 days per week  3 = 2-4 days per week  4 = 1-2 days per week  5 = 1-3 days per month  6 = Occasionally, usually less than once a month  7 = Never  Don’t know 777 | 1. Vegetable oil └──┘ 2. Lard or suet └──┘ 3. Butter or ghee └──┘ 4. Margarine └──┘ 5. Mixed butter + oil combination └──┘ 6. Other └──┘If Other, specify below   Other, please specify  ____________________________ | DIET_1q_1-6 | |
|  |  |  |  | DIET_1q_other | |
| R | | On average, how often do you eat meals that were **not prepared at a home**? (By meal, we mean breakfast, lunch or dinner)  1 = Daily = 1  2 = 5-6 days per week  3 = 2-4 days per week  4 = 1-2 days per week  5 = 1-3 days per month  6 = Occasionally, usually less than once a month  7 = Never  Don’t know 777 | └──┘ | DIET_1r | |
| S | | In a typical week, on how many days do you drink **sugar-sweetened beverages** (such as sodas, and other non-carbonated commercially prepared fruit drinks)?  Don’t know 777 | Number of days└─┴─┘ *If zero, go to SECTION 6* | DIET_1s | |
| T | | How many servings of **sweetened non-carbonated drinks** (ready to drink diluted cordials and syrups/commercially prepared sweetened fruit drinks) do you drink on a typical day? | | inst_diet2a | |

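### Five diet items ask for servings on a typical day where parallel items ask about an eating day, so weekly intake of foods not eaten daily may be misstated

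*Protocol*

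**What the plan says.** Section 5 (Behavioural measures – Diet) of the data collection tools pairs a frequency question with a quantity question for each food group. Fruit opens with "In a typical week, on how many days do you eat fruit". Its quantity item B then asks for servings on a typical day, with "do you eat on a typical day? (SHOWCARD 1") as the whole-fruit line. The same reference day appears for:

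- vegetables (item D), for example "How many servings of canned vegetables do you eat on a typical day"
- refined starch (item H): "How many servings of bread do you eat on a typical day"
- non-refined starch (item J): "How many servings of non-refined bread do you eat on a typical day"
- both halves of the sweetened-drinks item T: "do you drink on a typical day"

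Two items of the same design use another reference day. Item F asks "How many servings of tubers and high starch vegetables do you eat on one of those days", and item L (fish) uses the same phrase.

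The opening instruction of the section tells respondents to keep both a typical week and a typical day of the past month in mind. It does not say that the typical day is one on which the food is eaten. The document gives no rule for combining days with servings. Diet is listed among the behavioural measures collected at baseline and month 12 (Table 15) and appears in secondary outcomes d and i (section 3.9).

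**The concern.** A quantity question that follows a count of eating days should refer to those days, so that the two answers multiply to a weekly amount. Items F and L do this. Items B, D, H, J and T leave the reference day open. A person who eats fruit on two days a week could reasonably answer for a fruit day, for the average of all seven days, or for the usual day, which has no fruit.

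The absence of a scoring rule is not the complaint, since that may sit in a statistical analysis plan that is not at hand. The complaint is that no later rule can undo the ambiguity, because the form does not record which reading each respondent used.

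At stake is the measured change in diet. The error depends on how many days the food is eaten, and the intervention is meant to influence eating habits: supporting a healthy diet is an added care-companion task in the facility + community arm (section 3.3.3.1). Bias of this kind need not cancel between visits. The tools are also translated, so readings could differ between the three countries that the protocol hopes to combine.

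**Working it through.** **Inputs.** d = days per week the food is eaten (items A, C, G, I, S). s = servings on an eating day; the document gives no value, and the ratios below do not depend on it, so s = 2 serves as illustration. The document states no intake figure and no scoring formula, so there is nothing to reproduce. Two scoring rules are assumed: days × answer, and 7 × answer.

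**True weekly intake of a single food:** d × s.

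**Answer given under each reading of a typical day:**
- eating day: s
- average over all seven days: d × s / 7
- most usual day: 0 if d ≤ 3, s if d ≥ 4

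**Scored intake divided by true intake:**
- eating-day answer × d: (d × s)/(d × s) = 1, no error
- average-day answer × 7: (7 × d × s/7)/(d × s) = 1, no error
- average-day answer × d: (d × d × s/7)/(d × s) = d/7
- eating-day answer × 7: (7 × s)/(d × s) = 7/d
- most-usual-day answer: 0 under either rule when d ≤ 3; 1 (× d) or 7/d (× 7) when d ≥ 4

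| d | True, s = 2 | Average-day answer × d | Eating-day answer × 7 | Most-usual-day answer × d |
|---|---|---|---|---|
| 1 | 2 | 0.14 | 7.00 | 0 |
| 2 | 4 | 0.29 | 3.50 | 0 |
| 3 | 6 | 0.43 | 2.33 | 0 |
| 4 | 8 | 0.57 | 1.75 | 1.00 |
| 5 | 10 | 0.71 | 1.40 | 1.00 |
| 6 | 12 | 0.86 | 1.17 | 1.00 |
| 7 | 14 | 1.00 | 1.00 | 1.00 |

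**Change between visits.** Take s = 2 and a rise from 2 to 4 days. True intake goes from 4 to 8, a doubling.
- Average-day answer × d: 2 × (2 × 2/7) = 1.14, then 4 × (4 × 2/7) = 4.57, a fourfold rise.
- Eating-day answer × 7: 7 × 2 = 14 at both visits, no change.

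**Subtypes.** Items B, D, H, J and T split one group-level day count into several subtypes, whereas F and L ask for one quantity each. Suppose fruit is eaten on 4 days: 2 servings of whole fruit on 3 of them and 1 serving of dried fruit on the other. The truth is 3 × 2 + 1 × 1 = 7 servings a week.
- Amounts given only for the days each subtype is eaten: 4 × (2 + 1) = 12, too high.
- Amounts averaged over the 4 fruit days: whole 6/4 = 1.5, dried 1/4 = 0.25, and 4 × (1.5 + 0.25) = 7, correct.

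Copying the phrase from F and L is therefore not enough; the averaging has to be specified. The answer boxes for these items take two decimals, so such averages can be entered.

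**The case against.** The best defence is the layout. Each quantity item comes straight after a count of eating days and is skipped when that count is zero, so only people who eat the food are asked, by an interviewer. Many will answer for an eating day. If the analysis then multiplies by days, the reference-day error disappears. This stands, and it means that the error is possible, not established.

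A reader might infer that intake *is* misstated, by up to sevenfold. The document does not support that. Sevenfold needs a food eaten one day a week together with a mismatch between reading and scoring, and the scoring is not stated. Nor is sevenfold a limit, since the most-usual-day reading can record zero.

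A reader might also take this to undermine secondary objective 4. That objective concerns perceptions of behavioural risk factors, not amounts eaten; the link is to secondary outcomes d and i. Nor does the protocol plan a scale that combines these food groups with tubers and fish.

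Finally, both arms use the same form. If respondents in both arms read it alike and the intervention leaves intake unchanged, the wording alone creates no expected difference between arms. This also stands: the distortion shown above is in the size of a real change. It is no comfort where that change is the quantity to be estimated.

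**Conclusion.** The inconsistency is plain on the form: five quantity items use one reference day and two parallel items use another. For foods not eaten daily, weekly intake may be misstated by d/7, by 7/d, or recorded as zero, depending on how the respondent reads the question and how the answer is scored. The sizes rest on the assumed readings and scoring rules; how often each reading would occur cannot be known from the document. The error shrinks as eating becomes more frequent (0.86 or 1.17 at six days) and vanishes at seven.

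The effect is confined to amounts eaten, within secondary outcomes d and i. The days-per-week items are not affected by this wording and can be analysed alone. The HbA1c outcomes and the sample size are untouched. This is a cheap improvement to a secondary measure, not a threat to the trial's main conclusions.

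**What to change.** Before the form is used, reword items B, D, H, J and T to ask about one of the days on which the food group is eaten, as F and L do. Add an interviewer instruction to record, for each subtype, the average amount over those eating days, counting days without that subtype as zero. Weekly intake for the group is then days × the sum of the subtype servings. Weekly intake of a subtype should not be derived from servings reported only for the days on which that subtype is eaten.

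The cost is rewording, retranslation and brief interviewer training; averaging over eating days also asks a little more of the respondent. Question numbers and variable codes can stay as they are, which the instructions to site teams require. If baseline interviews have begun, keep each participant's wording the same at baseline and month 12 and flag the form version in the data. The trial would then hold two versions of the instrument, which is the main reason to make the change early.
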